### **Knowledge of husbands of MAGs regarding SRHR of MAGs**

The knowledge of husbands of MAGs on number of modern methods, and emergency contraceptive pill will be measured using two questions: i) which of the FP methods have you heard of; and ii) have you heard about emergency contraceptive pill. A continuous variable will be created for the first question based on the number of correct answers, while a binary variable will be created from the responses on the second question by recoding to '1=Yes' if the respondent heard of emergency contraceptive pill, and '0=No' otherwise.

The knowledge of husbands of MAGs regarding conception will be assessed using the following four questions: i) what is the appropriate age at first conception for a woman; ii) if a girl gets pregnant in her teenage years, what are the potential problems she might have to face; iii) after the birth of a child can a woman become pregnant before her menstrual period has returned; and iv) what are the consequences of not having proper spacing between two pregnancies. For questions i) and iii), separate binary variables will be created from the responses by recoding to '1=Yes' if it was a correct answer, and '0=No' otherwise. For questions ii) and iv), separate continuous variables will be created based on the number of correct answers.

A summative score will then be obtained by adding all the knowledge related variables, with a higher score indicating greater knowledge.

### **Positive attitudes of husbands of MAGs regarding SRHR**

Attitudes of husbands of MAGs regarding SRHR will be measured using six items, like “family planning is a women’s business and a man should not worry” and “a woman has right to choose when to first conceive”. The participants will report their agreement on a Likert scale (1 = strongly agree to 4 = strongly disagree). A summative score will be obtained, with a higher score indicating more positive attitude regarding SRHR.

**Positive attitudes regarding agency of MAGs regarding SRHR among their husbands**

Attitudes of husbands of MAGs about agency of MAGs regarding SRHR will be measured using 12 items. A typical example includes “It should be a wife’s decision when to have a child”. The participants will report their agreement on a 4-point Likert scale (1 = strongly agree to 4 = strongly disagree). A summative score will be obtained, divided into tertiles. Negatively valenced items will be reverse-coded, so higher score indicates more positive attitudes.

**Positive attitudes of husbands of MAGs regarding violence against women**

Attitudes of husbands of MAGs regarding violence against women will be measured using six items. A typical example includes “There are times when a woman deserves to be beaten”. The participants will report their agreement on a 4-point Likert scale (1 = strongly agree to 4 = strongly disagree). A summative score will be obtained, with a higher score indicating more positive attitudes.

**Positive attitudes of husbands of MAGs regarding gender roles within household**

Attitudes of husbands of MAGs regarding gender roles within household will be measured using three items. A typical example includes “Child care activities such as cleaning after toilet, giving bath is a mother’s responsibility”. The participants will report their agreement on a 4-point Likert scale (1 = strongly agree to 4 = strongly disagree). A summative score will be obtained, with a higher score indicating more positive attitudes.

**Knowledge of community member regarding SRHR of MAGs**

The community members’ knowledge on number of modern methods, and emergency contraceptive pill will be measured using two questions: i) which of the FP methods have you heard of; and ii) have you heard about emergency contraceptive pill. A continuous variable will be created for the first question based on the number of correct answers, while a binary variable will be created from the responses on the second question by recoding to ‘1=Yes’ if the respondent heard of emergency contraceptive pill, and ‘0=No’ otherwise.

The community members’ knowledge regarding conception will be assessed using the following four questions: i) what is the appropriate age at first conception for a woman; ii) if a girl gets pregnant in her teenage years, what are the potential problems she might have to face; iii) after the birth of a child can a woman become pregnant before her menstrual period has returned; and iv) what are the consequences of not having proper spacing between two pregnancies. For questions i) and iii), separate binary variables will be created from the responses by recoding to ‘1=Yes’ if it was a correct answer, and ‘0=No’ otherwise. For questions ii) and iv), separate continuous variables will be created based on the number of correct answers.

A summative score will then be obtained by adding all the knowledge related variables, with a higher score indicating greater knowledge.

**Positive attitudes of community members regarding SRHR**

Attitudes of community members regarding SRHR (FP and conception) will be measured using six items, like “family planning is a women’s business and a man should not worry” and “a woman has right to choose when to first conceive”. The participants will report their agreement on a Likert scale (1 = strongly agree to 4 = strongly disagree). A summative score will be obtained, with higher score indicating more positive attitude regarding SRHR.

**Positive attitudes regarding agency of MAGs regarding SRHR among their husbands**

Attitudes of community members about agency of MAGs regarding SRHR will be measured using 12 items. A typical example includes “It should be a wife’s decision when to have a child”. The participants will report their agreement on a 4-point Likert scale (1 = strongly agree to 4 = strongly disagree). A summative score will be obtained, divided into tertiles. Negatively valenced items will be reverse-coded, so higher score indicating more positive attitudes.

**Positive attitudes of husbands of MAGs regarding violence against women**

Attitudes of community members regarding violence against women will be measured using six items. A typical example includes "There are times when a woman deserves to be beaten". The participants will report their agreement on a 4-point Likert scale (1 = strongly agree to 4 = strongly disagree). A summative score will be obtained, with higher score indicating more positive attitudes.

#### **Positive attitudes of husbands of MAGs regarding gender roles within household**

Attitudes of community members regarding gender roles within household will be measured using three items. A typical example includes "Child care activities such as cleaning after toilet, giving bath is a mother's responsibility". The participants will report their agreement on a 4-point Likert scale (1 = strongly agree to 4 = strongly disagree). A summative score will be obtained, with higher score indicating more positive attitudes.

#### **Community social norms related to consent and choice of MAGs regarding their SRH**

We will measure Social norms around consent and choice of MAGs in SRH following Cialdini (1998) and Bicchieri (2006, 2012) [32-34]. The statements to capture social norms around consent and choice of MAGs regarding their SRH will be framed considering Cialdini's (1998) and Bicchieri's (2006, 2012) theory of social norms and validated for the target population. The theory of social norms is a theory of what motivates collective patterns of behavior. It tries to answer a very basic question – why do people do what they do? The key concepts in this theory include empirical and normative expectations.

Empirical expectations refer to "What most people in her/his village will do in a specific circumstance." A typical example includes: "Do you strongly agree/agree/disagree/strongly disagree with this statement - Most of the married adolescent girls in your village achieve their aspiration regarding their desired method of contraception".

Normative expectations refer to "What most people in her/his village expect others to do in a specific circumstance." A typical example includes: "Do you strongly agree/agree/disagree/strongly disagree with this statement - Most of the husbands of married adolescent girls in your village will approve if their wives try to achieve their aspiration regarding their desired method of contraception".

Social norms around SRHR of MAGs in the domains such as FP, conception, number of children to have, abortion and SRH service uptake will be assessed using data from the MAG and community surveys. A set of statements will be used to assess the participants' level of agreement collected on a Likert scale (1 = totally disagree to 4 = totally agree). A scale will be constructed and validated using factor analysis. A summative score will be obtained, with a higher score indicating stronger positive social norm.

### **Data Analysis**

Describe plans for data analysis, including stratification by sex, gender and diversity. Indicate whether data will be analysed by the investigators themselves or by other professionals. Specify what statistical software packages will be used and if the study is blinded, when the code will be opened. For clinical trials, indicate if interim data analysis will be required to determine further course of the study.

### **Quantitative data analyses**

Items in the survey questionnaires will be recoded so that all are anchored at 0. For example, for gender norms and attitudes, each item with scores ranging between 1 and 4 in the questionnaire will be recoded to 0–3. Negatively valenced items will be reverse-coded, so higher score indicates positive outcome. All the measurement scales used in the study will be validated using factor analysis. This exercise will allow us as well to reduce the number of items in the scales. Internal consistency (or reliability) of a scale will be measured using Cronbach's alpha. A scale with alpha equal to 0.60 or more will be considered acceptable. Scale validity will be measured using the Kaiser-Meyer-Olkin (KMO) test, where KMO equal to 0.60 or more will be considered acceptable. Once the final scale is constructed, a summative score will be obtained for each scale, and the scores will then be divided into tertiles.

During baseline we will explore the current situation in empowerment and SRHR among MAGs and their correlates, while at end line we will measure the impact of the social norms intervention on empowerment, on social norm change and promotion of demand, access and positive practices in relation to SRHR among the MAGs. Using the baseline survey data, the basic background characteristics (e.g., age, education,

religion, ethnic group) of the girl and community samples will be compared by arm (control, treatment) to check the arm balance. Descriptive analyses will be performed to report frequencies and percentages of different outcomes of interest. Chi-square, ANOVA and t-tests will be performed to check whether the study arms are covariate balanced. Linear and logistic regression analyses will be performed to identify the underlying factors for current situation in SRHR among MAGs.

Intention-to-treat (ITT) analysis will be used during assessing the impact of the intervention. Thus, all the MAGs enrolled at baseline and could be successfully interviewed at endline will be included in the analysis irrespective of their actual level of participation in the intervention activities. The information on participation of study participants in the intervention activities will come from the programme monitoring data and will also be used in the models. The impact of the intervention on primary and secondary outcomes will be assessed using risk ratios/regression coefficients derived from binary/linear regression analyses for measuring change in outcomes in the intervention arms relative to change in the control arm. Significance level will be set at  $p < .05$  for all analyses. The data will be analysed using STATA 16.

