### **Sample Size Calculation and Outcome (Primary and Secondary) Variable(s)**

Clearly mention your assumptions. List the power and precision desired. Describe the optimal conditions to attain the sample size. Justify the sample size that is deemed sufficient to achieve the specific aims.

The sample size for the survey of MAGs was calculated based on the primary outcomes "ability of a MAG to achieve own choice regarding: (1) FP use; (2) conception; and (3) SRH service uptake". Considering a cluster size of 22 married adolescent girls and their husband, and assuming a 50% prevalence rate of ability of a MAG to achieve own choice in SRH issues among this group (as unknown), 15% effect size, an Intra-Cluster Correlation of 0.05, 5% significance level and 80% power we required 16 clusters per arm making the total number of clusters 32. Considering a 10% non-response rate at baseline, 20% refusal rate among MAGs interviewed at baseline to participate in the intervention, and another 15% drop out rate at endline among the MAGs participated in the intervention, the group size increased to 35 and total sample size increased to 1,120 MAGs. As these considerations provided us with the maximum sample size, this current sample size will allow us to measure the changes in all other secondary outcomes of the study.

The husband of the selected MAGs will also be included in the study to measure the secondary outcomes related to their knowledge and attitudes regarding SRHR relevant to them and the MAGs.

To assess social norm change we focused on social norms around the MAGs' consent and choice in SRH. We will assess this change surveying adult community members aged 35-59 years. Since the prevalence of positive social norms around consent and choice in SRH issues is unknown among this population we assumed it as 50%. Considering a 15% effect size, 5% significance level, 80% power and 5% non-response rate, we required 540 community members (270 females and 270 males) from 32 clusters. Dividing the numbers by number of clusters and then rounding up the total sample size increased to 576 (nine females and nine males from each cluster).

The qualitative sample size includes 6 KIIs, 32 IDIs and 8 FGDs at baseline and endline.

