| 19                        | Positive attitudes regarding agency of MAGs regarding SRHR among the community members                                                   |      |                  | √                 |
| 20                        | Positive attitudes of community members regarding violence against women                                                                 |      |                  | √                 |
| 21                        | Positive attitudes of community members regarding gender roles within household                                                          |      |                  | √                 |
| 22                        | Positive social norms regarding SRHR of MAGs                                                                                             | √    |                  | √                 |

**Instrumental agency of MAGs in decision making regarding SRHR (i.e., FP use; timing of first conception; and number of children to have)**

The MAGs will be asked about the main decision maker regarding: (a) FP use; (b) timing of first conception; and (c) number of children to have. The response options included '1=the MAG herself', '2=husband', '3=jointly' and '4=someone else'. A follow up question, 'what kind of joint decision it was', was asked if the response was 'jointly'. The response options included '1=he voiced his choice and I agreed', 'he voiced choice and forced me to agree', and '3=I voiced my choice and he agreed'. A MAG will be considered agentic in decision making regarding a specific theme of SRHR and will be coded as 'Yes=1' if she decided herself or it was a joint decision without any force on her, and 'No=2' otherwise. We will generate a summative score, with a higher score indicating higher agency.

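### Every scale score is to be cut into tertiles, although most outcomes are defined as uncut sums and the named models are linear or binary; wherever tertiles enter the impact analysis, information is lost for no stated gain

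*Protocol*

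**What the plan says.** - **General rule.** Under Quantitative data analyses, after recoding, factor analysis and reliability checks, "a summative score will be obtained for each scale, and the scores will then be divided into tertiles". No exception is made, and the step is not limited to description.
- **Two outcome definitions repeat it.** For husbands' attitudes to girls' agency (outcome 14 in Table 2): "A summative score will be obtained, divided into tertiles". The definition for community members (outcome 19, printed under the same husbands' heading) has the same step.
- **Most other scale definitions do not.** Intrinsic, instrumental and collective agency, critical consciousness, the attitude scales of all three groups and social norms are described as scores on which higher is better, with no cut.
- **Models.** Effects are to be expressed as "risk ratios/regression coefficients derived from binary/linear regression analyses", measuring change in the intervention arm relative to change in control. No ordinal model is named.
- **Primary outcome.** Three decisions, "a) FP use; (b) timing of first conception; and (c) number of children to have", are each coded yes or no and then added: "We will generate a summative score, with a higher score indicating higher agency". Tertiles are not mentioned there.

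**The concern.** The protocol gives two descriptions of the same outcomes: a sum, and a three-level grouping of that sum. The models fit the sum directly. They accept the grouping only after a further choice that is not stated: equal spacing of the levels, or a decision on which two to merge. For a given scale an analyst could report a mean difference, a trend across tertiles, or a risk ratio for the top or bottom tertile, and each could claim support in the text.

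Two things are at stake. Grouping a many-valued score discards information, so a real effect is harder to detect. The effect also becomes a shift across cut points that depend on the sample, where score points would have a fixed meaning. The protocol does not say which data set the cut points.

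**Working it through.** **1. The plan's own sizing, for reference.** Inputs from the sample size section: 50% prevalence, 15% effect (read as 50% against 65%), ICC 0.05, 22 girls per cluster, 5% significance (two-sided assumed), 80% power.
- Two proportions, no continuity correction: (1.960·√0.48875 + 0.8416·√0.4775)² / 0.15² = 169.3, so 170 per arm.
- Design effect 1 + 21 × 0.05 = 2.05; 170 × 2.05 = 348.5; 348.5 / 22 = 15.84, so 16 clusters per arm.

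The stated 16 clusters per arm reproduces. It rests on a binary outcome, not on a scale score.

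**2. Information kept after tertiling.** Assumption, not in the protocol: a roughly normal score and a small shift between arms. The upper cut is c = Φ⁻¹(2/3) = 0.4307, with density φ(c) = 0.3636. Relative to the uncut score:
- Tertiles scored 0/1/2: (2φ(c))² / (2/3) = 0.793, a loss of 20.7%.
- Top tertile against the rest: φ(c)² / (2/9) = 0.595, a loss of 40.5%.

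Simulated sums of 3, 6, 12 and 29 four-point items gave losses of about 15–20% and 37–43%, so exact normality is not critical.

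**3. Power, design effect unchanged by cutting.** Start from a scale with exactly 80% power uncut: 1.960 + 0.8416 = 2.8016.
- 0/1/2 scores: Φ(2.8016·√0.793 − 1.960) = 70.4%. Restoring 80% takes 16 / 0.793 = 20.2, so 21 clusters per arm.
- Top tertile: Φ(2.8016·√0.595 − 1.960) = 58.0%. Restoring 80% takes 16 / 0.595 = 26.9, so 27 clusters per arm.

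**4. Power if cutting also lowers the ICC.** Suppose village effects act on the uncut score, with ICC 0.05. Cutting then shrinks the ICC by about the same factor as the information, and part of the loss is recovered.
- 0/1/2 scores: ICC 0.05 × 0.793 = 0.0397; design effect 1 + 21 × 0.0397 = 1.833; information kept 0.793 × 2.05 / 1.833 = 0.887; power 75.1%.
- Top tertile: ICC 0.05 × 0.595 = 0.0297; design effect 1.625; information kept 0.595 × 2.05 / 1.625 = 0.751; power 68.0%.

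A simulation of clusters of 22 gave 0.89 and 0.75.

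**5. Primary score.** Three yes/no items give four possible values. At 50% per item and independence the shares are 12.5/37.5/37.5/12.5%, and the closest three groups are 50/37.5/12.5%. With 65% per item and latent correlation 0.2, merging the two lowest values gives 30/37/33%. With 50% and latent correlation 0.8, merging the two middle values gives 35/31/35%. Near-equal thirds are therefore possible but not guaranteed.

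**6. Cut points remade each round.** If each round is cut on its own pooled sample, about one third falls in the top group every time. With equal arms, an intervention share of 1/3 + x forces a control share of 1/3 − x. A rise common to both arms vanishes, and a gain in one arm appears as a decline in the other.

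**The case against.** The strongest reply is that the protocol never says tertiles are the analysed outcome. Linear regression on the sums fits the stated models, and tertiles could serve the planned tables of frequencies and percentages. This stands in part: the loss is conditional. It does not remove the problem, because the general rule has no such limit, and for outcomes 14 and 19 the cut is part of the outcome definition.

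Four stronger readings are tempting, and the protocol does not support them.
- *The primary outcome cannot be put into tertiles.* Its definition has no tertile step. It is not called a scale, and the rule applies to scales built after factor analysis. Three groups can always be formed from four values.
- *Power is lost on nearly all outcomes.* About 14 of the 22 outcomes are multi-item agency, attitude, consciousness or norm scales. Knowledge, communication and negotiation counts are not clearly covered, and service uptake and partner violence are reported as percentages or yes/no.
- *Results are not comparable across rounds.* That assumes cut points are remade each time. The protocol does not say so, and this detail may sit in an analysis plan.
- *The sample size is undermined.* The trial is sized on a binary outcome. A 15-point rise in a top tertile, 33.3% to 48.3%, has variance sum 0.222 + 0.250 = 0.472, slightly below the 0.250 + 0.2275 = 0.4775 for 50% to 65%. The loss is measured against the uncut score, not against the stated sizing.

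**Conclusion.** The point holds as an internal inconsistency with an avoidable cost. The tertile rule conflicts with most of the scale definitions and sits awkwardly with the named models.

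Where tertiles enter the impact analysis, the loss at individual level is about 21% (0/1/2 scores) to about 40% (top tertile against the rest). Power of 80% on the uncut score falls to about 70% or 58% with the design effect unchanged, or to about 75% or 68% if the ICC shrinks with the cut. These figures assume a near-normal score, a small shift and, for the second pair, ICC 0.05 with 22 per cluster. Distortion of change over time arises only if cut points are remade at each round. For the primary score the finding is only that the reach of the rule is unclear. This is a free improvement, not a flaw that invalidates the design.

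**What to change.** In Quantitative data analyses, and in the definitions of outcomes 14 and 19:
- State that impact analyses use the uncut summed score, reported as a difference in means from a model that accounts for clusters.
- State that the primary outcome is analysed as the 0–3 score, so that the tertile rule plainly does not apply to it.
- Limit tertiles to descriptive tables, with cut points fixed once on pooled baseline data and used unchanged at endline.

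The cost is a few sentences. No extra data, sample or fieldwork is needed, and the linear regression already named covers the scores once clustering is accounted for.

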### **Cluster formation and randomization,**

The villages from Rajbari Sadar upazila will be treated as clusters or the primary sampling units in this study. The list of villages and the number of households in each village will be obtained from the upazila statistics office. Any village/cluster with approximately 500 or more households will be considered eligible to be included in the study for allowing an adequate number of MAGs. Three teams, each consisting of two members, will visit each of the eligible villages, talk to local people, check which could be selected as study clusters and which could be potential buffers. All the teams will then finalize the list of eligible villages after ensuring sufficient buffer zone.

We will then randomly select 32 clusters/villages from the list of eligible villages. The selected 32 clusters will be subsequently assigned randomly to either the intervention or control group in a 1:1 ratio. The randomization process will be carried out by an independent statistician from icddr,b who will not be involved in the designing the study, recruiting the study participants, implementing the intervention or analysing the data.

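### The baseline balance check names chi-square, ANOVA and t-tests with no allowance for villages, so it would flag a correctly randomised trial as unbalanced too often

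*Protocol*

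**What the plan says.** The protocol's section on quantitative data analyses plans that background characteristics, with age, education, religion and ethnic group as examples, "of the girl and community samples will be compared by arm (control, treatment) to check the arm balance". It then names the tool: "Chi-square, ANOVA and t-tests will be performed to check whether the study arms are covariate balanced". The same section sets one threshold, p < .05, for all analyses ("Significance level will be set at"). It does not mention clustering, village summaries or standardised differences for this check.

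The unit of randomisation is the village: "The selected 32 clusters will be subsequently assigned randomly to either the intervention or control group in a 1:1 ratio". The sample size section allows for correlation within villages: "an Intra-Cluster Correlation of 0.05, 5% significance level and 80% power we required 16 clusters per arm making the total number of clusters 32".

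Two further points bear on the check. According to the section on household enumeration, sampling and recruitment, enumeration, selection, consent and enrolment all follow allocation. The blinding section says that nobody is blinded during selection and allocation.

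**The concern.** A standard chi-square, ANOVA or t-test treats each respondent as an independent observation. Here whole villages are allocated, and people in one village tend to resemble each other. The difference between arms therefore varies more by chance than these tests assume, and they reject too often even when allocation was sound.

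There is a second, separate weakness. The stated aim is to learn whether the arms are balanced. A p-value says whether a difference exceeds what the test regards as chance. It does not say how large the difference is, and a difference that gives p > .05 is not thereby negligible.

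At stake is a statement in the baseline report. The report could say that the arms are not balanced when randomisation worked, or it could raise an alarm that nobody can interpret.

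**Working it through.** **The plan's own figure.** The inputs are 50% against 65%, a 5% level, 80% power, an ICC of 0.05 and 22 girls per village.
- A two-proportion calculation without clustering gives 170 girls per arm.
- Design effect: 1 + (22 − 1) × 0.05 = 2.05.
- 170 × 2.05 = 348.5, and 348.5 / 22 = 15.84, so 16 villages per arm, as stated.

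The sample size thus counts village correlation. The balance check does not mention it.

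**Inputs for the balance check.**
- 16 villages per arm (cluster formation and randomization).
- Girls: 35 selected per village less 10% baseline non-response, so 35 × 0.90 = 31.5 interviewed.
- Community sample: 9 women + 9 men = 18 per village.
- Level 0.05, taken as two-sided because the protocol does not state sidedness.
- ICC 0.05. The protocol states this for the outcome. Its use for covariates is an assumption, so a range is shown.

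**Formula.** For a test that ignores villages, under correct randomisation:

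false-flag rate = 2 × [1 − Φ(1.96 / √DE)], with DE = 1 + (m − 1) × ICC.

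| Sample | m | ICC 0.01 | ICC 0.02 | ICC 0.05 | ICC 0.10 | ICC 0.20 |
|---|---|---|---|---|---|---|
| Girls, after non-response | 31.5 | 8.6% | 12.2% | 21.7% | 33.0% | 46.2% |
| Girls, all selected | 35 | 9.0% | 13.0% | 23.3% | 35.0% | 48.3% |
| Community | 18 | 7.0% | 9.0% | 15.0% | 23.3% | 35.0% |

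At ICC 0.05 the design effects are 2.525, 2.70 and 1.85.

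**Check by simulation.** In 10,000 trials per setting with 16 villages per arm, no true difference and ICC 0.05:

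| m | t-test on individuals | Chi-square on individuals | t-test on village means |
|---|---|---|---|
| 32 (girls) | 21.7% | 22.1% | 5.1% |
| 18 (community) | 14.7% | 15.9% | 4.8% |

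The village-level test holds its nominal rate, so the excess comes from the choice of test and not from the allocation.

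**Several covariates.** For four independent covariates in girls at ICC 0.05, 1 − (1 − 0.22)⁴ ≈ 63%. The benchmark for four valid 5% tests is 1 − 0.95⁴ = 18.5%.

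**What the flag means in size.** There are 16 × 31.5 = 504 girls per arm. The unadjusted test flags a standardised difference above about 1.96 × √(2/504) = 0.12. The true chance standard deviation of that difference at ICC 0.05 is √(2 × 2.525/504) = 0.10. A flag can therefore arise from a difference only slightly larger than one chance standard deviation.

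These results are for a continuous or two-category covariate. Covariates with more categories were not computed.

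**The case against.** **The unit of analysis is not stated.** The protocol names test families and survey samples. It neither says that the tests run on individuals nor rules out cluster adjustment, and an analysis plan not available here could settle this. That is true. However, the named tests in their standard form, applied to samples of respondents with no adjustment mentioned, are most naturally read as individual-level tests, and the protocol does prescribe them.

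**The ICC belongs to the outcome.** No ICC is given for any covariate. At 0.01 the excess is modest. This stands: the size depends on an assumption, although the direction is the same for any positive ICC.

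**Testing could be useful here.** A reader might infer that randomisation already settles the null, so that any baseline test, even one adjusted for clusters, is pointless. The document does not support that. Consent and eligibility, including the stated intention not to migrate, are established after unblinded allocation, so recruitment could differ by arm. Random selection of the 35 girls by an independent statistician limits this but does not remove it. A village-level test has a meaningful null and holds about 5%. The unadjusted tests cannot serve that purpose, because they confuse selection with ordinary village variation.

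**Nothing depends on the check.** No section ties covariate adjustment, a decision or the impact model to these tests. This stands and limits the consequence.

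**Conclusion.** The point holds in limited form. As written, the balance check would over-report imbalance: about 22% per covariate for girls and 15% for the community sample, against 5%. This rests on the individual-level reading and on covariates sharing the outcome's ICC of 0.05. For girls the range is about 8 to 9% at ICC 0.01 and 33 to 35% at 0.10. The 63% for at least one flag also needs four independent covariates and should always be read beside 18.5%.

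Two stronger conclusions might be drawn, and the document supports neither.
- *The tests will bias the effect estimate or drive the choice of adjustment covariates.* The protocol states no such link.
- *The baseline primary score is left out of the check.* The list of characteristics is only illustrative. Descriptive reporting of outcomes is planned, and the impact analysis compares change in outcomes between arms.

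The harm is a false or uninterpretable statement about baseline balance.

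**What to change.** In the section on quantitative data analyses, replace the sentence that names the three tests with:

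*Baseline characteristics and baseline values of the primary outcome will be tabulated by arm with standardised differences, and balance will be judged from their size and direction, without individual-level significance tests; if any test is kept to look for differential recruitment, it will be done on village summaries or with adjustment for village clustering.*

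The standardised differences should be read against the chance spread that 16 villages per arm produce (about 0.10 for girls at ICC 0.05).

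The cost is one sentence of wording. It needs no new data and no more participants, and it loses only a column of unadjusted p-values. How covariates are chosen for any adjusted model can be left to the statistical analysis plan.
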